**If the screening and Day 0 visits occur within 24 hours, no procedures need to be repeated.**

Participants must complete the following assessments before administering the study drug (if not done in the previous 24 hours):

- Physical examination including, vital signs (heart rate, temperature, blood pressure, and body weight).
- Documentation of respiratory status:
- Respiratory Rate
- SpO2 at rest or PaO2
- FIO2
- Oxygen supplementation:
  - nasal cannula
  - high flow oxygen therapy
  - mask with a reservoir bag
  - non-invasive ventilation
- Radiographic findings if available.
- Obtain blood samples for:
- Hematology and coagulation: Hematocrit, Hemoglobin, Mean Corpuscular Hemoglobin Concentration (MCHC), MCV (Mean Corpuscular Volume), Platelets, Red blood cells, White blood cells with differential (Basophils, Eosinophils, Lymphocytes, Monocytes, Neutrophils). **D-Dimer.**

# Chemistry: Glucose (fasting or non-fasting), Urea, Creatinine, Sodium, Potassium, Calcium, Chloride, Total Protein, Albumin, Bilirubin (total and direct), Aspartate Aminotransferase (AST), Alanine Aminotransferase (ALT), Lactate Dehydrogenase (LDH), Ferritin, C-reactive Protein (CRP) , troponin.

# Markers of Immunological function: Immunoglobulins, serum cytokines (IL-6, IL-1, TNFa, IFNb, IL-10); T cell repertoire: CD3 (CD4, CD8), naive CD45RA+CD27+, central memory CD45RA-CD27+, effector memory CD45RA-CD27- y EMRA CD45RA+CD27-, Activated T cells (HLADR+), T regs (CD4+CD25+CD127low), Tgd; NK cells repertoire CD56+CD3- (KIR (2DL1, 2DL2/3, 3DL1), NCR (NKp30, NKp44, NKp46), NKG2D); NKT cells, B cells, memory B cells (CD19+CD27+).

# Additional investigational studies: Blood samples will be stored for research use. These samples will be processed to obtain the cells and a phenotypic study will be carried out to see the recovery in time of immunological markers using the flow cytometry technique. The functionality of infected COVID-19 cells and recovered cells will be studied by co-culture assays to see cytokine secretion by flow cytometry. In addition, plasma cytokines will be studied by protein assays.

- Pregnancy test (for women of childbearing potential).
- Record any serious adverse events and all adverse events related to protocol-mandated procedures occurring after signing the consent form.

## Daily Study Assessments

The following evaluations are to be completed daily from Days 1 – 90 or until discharge, whichever occurs earlier (these will be performed as far as possible considering the increased work-load):

- Physical examination including, vital signs (heart rate, temperature, blood pressure).
- Documentation of respiratory status:
- Respiratory Rate
- SpO2 at rest or PaO2
- FIO2
- Oxygen supplementation:
  - nasal cannula
  - high flow oxygen therapy
  - mask with a reservoir bag
  - non-invasive ventilation
  - mechanical ventilation, or ECMO.
- Radiographic findings **if available**.
- **Scales (NEWS and 7-point scale).**
- Review AEs and document concomitant medications.

## Additional Assessments

## Will be performed as far as possible considering the increased work-load and if the investigator considers it appropriate:

- SARS-CoV-2 testing by PCR: Days 7, 14, 21, 28 and 90 or until a negative result is obtained, whichever occurs first.
- Blood samples for:
- Hematology and Chemistry: Day 3, 7, 14, 21, 28.

# Markers of Immunological function: Performed weekly.

- Donor chimerism: Day 3 and 7. If donor chimerism persists by day 7, repeat, 14, 21, 28 or until disappearance (weekly until disappearance).

# Additional investigational studies: Days 3, 7, 14, 21 and 28. Blood samples will be stored for research use. These samples will be processed to obtain the cells and a phenotypic study will be carried out to see the recovery in time of immunological markers using the flow cytometry technique. The functionality of infected COVID-19 cells and recovered cells will be studied by co-culture assays to see cytokine secretion by flow cytometry. In addition, plasma cytokines will be studied by protein assays.

- The first 18 patients will be followed for possible DLTs during the 21 days following cell infusion.

## Schedule of activities phase I

Table 2: Schedule of activities Phase I

| All the visits have a window of +/- 1 day | **Screening/D0** | **D1-D90 or until discharge** | **D7** | **D 14** | **D 21** | **D 28** | **D 90** |
| --- | --- | --- | --- | --- | --- | --- | --- |
| **Informed Consent** | x |  |  |  |  |  |  |
| **SARS-CoV-2 PCR testing** |  |  | x | x | x | x | x |
| **Medical history** | x |  |  |  |  |  |  |
| **Concomitant medications** | x | x | x | x | x | x | x |
| **Physical examination** | x | x | x | x | x | x | x |
| **Vital signs** | x | x | x | x | x | x | x |
| **Respiratory status** | x | x |  | x | x | x | x |
| **Hematology** | x | X^3^(day 3) | x | x | x | x |  |
| **Biochemistry** | x | X^3^(day 3) | x | x | x | x |  |
| **Markers of immunological function^1^** | x |  | x | x | x | x | x |
| **Blood sample for additional investigational studies** | x | X (day 3) | x | x | x | x |  |
| **Donor chimerism** |  | X^2^(day 3) |  | X^2^ | X^2^ | X^2^ |  |
| **Pregnancy test** | x |  |  |  |  |  |  |
| **Scales (NEWS and 7 point scale)** | x | x | x | x | x | x | x |
| **Improvement according to investigator/Second dose**** |  |  | x |  |  |  |  |
| **DLTs** | x | | | | |  |  |
| **Evaluation of patient recovery** |  |  |  | x |  |  |  |
| **Adverse events** | X | | | | | | |

^1^ Performed at screening and weekly. Please review section 7 for specific assessments.

^2^ Days: 3 and 7. If donor chimerism persists by day 7, repeat on days 14, 21, 28 and then continue weekly (until disappearance) Stop once it’s negative.

^3^Day 3

^**^ Those patients showing clinical improvement at day 7 according to the investigator (based on respiratory status and blood-test result) who haven’t shown previous toxicities of grade 3 or higher **and** if donor chimerism doesn´t persist, can receive a second cycle with the same dose at Day 7, if the investigator considers it appropriate.

## Schedule of activities phase II

Table 3: Schedule of activities Phase II

| All the visits have a window of +/- 1 day | **Screening/D0** | **D1-D90 or until discharge** | **D7** | **D 14** | **D 21** | **D 28** | **D 90** |
| --- | --- | --- | --- | --- | --- | --- | --- |
| **Informed Consent** | x |  |  |  |  |  |  |
| **SARS-CoV-2 PCR testing** |  |  | x | x | x | x | x |
| **Medical history** | x |  |  |  |  |  |  |
| **Concomitant medications** | x | x | x | x | x | x | x |
| **Physical examination** | x | x | x | x | x | x | x |
| **Vital signs** | x | x | x | x | x | x | x |
| **Respiratory status** | x | x |  | x | x | x | x |
| **Hematology** | x | X^3^ (day 3) | x | x | x | x |  |
| **Biochemistry** | x | X^3^ (day 3) | x | x | x | x |  |
| **Markers of immunological function^1^** | x |  | x | x | x | x | x |
| **Blood sample for additional investigational studies** | x | X (day 3) | x | x | x | x |  |
| **Donor chimerism** |  | X^2^ (day 3) | x | X^2^ | X^2^ | X^2^ |  |
| **Pregnancy test** | x |  |  |  |  |  |  |
| **Scales (NEWS and 7 point scale)** | x | x | x | x | x | x | x |
| **Evaluation of patient recovery** |  |  |  | x |  |  |  |
| **Improvement according to investigator/Second dose^**^** |  |  | x |  |  |  |  |
| **Adverse events** | x | | | | | | |

^1^ Performed at screening and weekly. Please review section 7 for specific assessments.

^2^ Day: 3 and 7. If donor chimerism persists by day 7, repeat on days 14, 21, 28 and then continue weekly (until disappearance). Stop once it is negative.

^3^Day 3

^**^ Those patients showing clinical improvement at day 7 according to the investigator (based on respiratory status and blood-result tests) who have not shown previous toxicities of grade 3 or higher **and** if donor chimerism doesn´t persist, can receive a second cycle with the same dose at Day 7, if the investigator considers it appropriate.

## Follow-up

Patients will be followed up until day 90, discharge or death, whichever occurs earlier. However, if the patient is discharged before day 30, weekly ambulatory visits (days 7, 14, 21 and 28) will be performed if the investigator considers it appropriate.

Donor chimerism will be evaluated on days specified in the schedule of assessments and weekly until disappearance in all patients.

If the patient has been discharged before day 30 they will be contacted by phone at Day 30 and Day 90 to obtain information about evolution and adverse events.

Patients discharged after day 30 will be contacted by phone at Day 90 to obtain information about evolution and adverse events.

**End of study:** The end of study date will be the date of the last visit of the last patient included.

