**Phase I:**

Patients with SARS-CoV-2+ pneumonia or lymphopenia **and** O_2_Sat ≤ 94% on room air at screening, with no oxygen requirement or with an oxygen need of **≤ 2.5 lpm** in nasal cannula, will be selected.

This phase has a single ascending dose design with up to 3 planned dose levels:

- **Arm A:** patients will receive memory T cells:
  - Cohort 1: Starting dose will be up to 1x10^5^/kg
  - Cohort 2: 1x10^5^/kg to 5x10^5^/kg
  - Cohort 3: 5x10^5^/kg to 1x10^6^/kg
- **Arm B:** patients will receive NK cells:
  - Cohort 1: starting dose will be up to 1x10^6^/kg
  - Cohort 2: 1x10^6^/kg to 5x10^6^/kg
  - Cohort 3: 5x10^6^/kg to 1x10^7^/kg

Additionally to the investigational product, all patients will receive the local standard of care for COVID-19 treatment.

The next cohort will open if all the patients in the previous cohort have been included and no safety issues have aroused during the follow-up after cell infusion (data of at least 7 days after cell infusion is required to proceed to each subsequent dose).

Those patients showing clinical improvement at day 7 according to the investigator (based on respiratory status and blood-test results) who haven’t shown previous toxicities of grade 3 or higher, can receive a second cycle with the same dose at Day 7, if the investigator considers it appropriate.

The 18 patients in the Phase I will continue to be followed for possible DLTs during the 21 days following cell infusion.

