## Graft-versus-host disease

## Graft-versus-host disease (GVHD) is a condition where the immune system of the donor attacks the recipient’s tissues and may range from mild to very severe. It can involve skin, liver and gastrointestinal tract in the acute phase and may become chronic causing dry mouth, dry eyes or skin changes. Considering the characteristics of the investigational products in this protocol we expect the incidence of clinically significant GVHD (grade III to IV) to be very low (<1%).

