**Administration dose and Schedule:**

1. **Single Ascending Dose Cohorts (Phase I)**

All patients will receive the SoC of each site for COVID19. Additionally, they will receive the investigational treatment.

**Arm A:** If one or more HLA class I match between donor and recipient is present, patients will receive memory T cells.

- Cohort 1: starting dose will be up to 1x10^5^/kg.
- Cohort 2: 1x10^5^/kg to 5x10^5^/kg
- Cohort 3: 5x10^5^/kg to 1x10^6^/kg.

**Arm B:** If donor and recipient have less than one HLA class I match or HLA-KIR mismatch, they will receive NK cells.

- Cohort : starting dose will be up to 1x10^6^/kg
- Cohort 2: 1x10^6^/kg to 5x10^6^/kg.
- Cohort 3: 5x10^6^/kg to 1x10^7^/kg.

The next cohort will open if all the patients in the previous cohort have been included and no safety issues have aroused during the follow-up after cell infusion (data of at least 7 days after cell infusion is required to proceed to each subsequent dose).

Those patients showing clinical improvement at day 7 according to the investigator (based on respiratory status and blood-result tests) who haven’t shown previous toxicities of grade 3 or higher, can receive a second cycle with the same dose at Day 7, if the investigator considers it appropriate.

The 18 patients included in the Phase I will continue to be followed for possible DLTs during the 21 days following cell infusion.

1. **Dose level decisions for Phase II** will be guided by safety and DLT data from Phase I. Phase II will begin once RP2D is established based on Phase I data.

The recommended dose will be the maximum tolerated dose (MTD) unless no MTD is determined in the dose escalation segment of the study. In this situation, the recommended dose will be the highest dose evaluated in the dose escalation segment.

Those patients showing clinical improvement at day 7 according to the investigator (based on respiratory status and blood-result tests) who haven’t shown previous toxicities of grade 3 or higher, can receive a second cycle with the same dose at Day 7, if the investigator considers it appropriate.

Third party donors will be individuals in recovery phase, with no symptoms for at least 14 days and at least one SARS-CoV-2 negative test. The blood donor selection will be done by the Regional Blood Transfusion Center. Refer to "donor selection criteria" in section 5 for further details.

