## Subject Treatment Assignment

Patients will be allocated into two groups: Arm A and Arm B depending on HLA typing.

For the phase I, patients on each arm will subsequently undergo a correlative allocation into the different cohorts (1,2,3).

The decision to proceed to each subsequent dose level (next cohort) will be made based on safety and tolerability data from the prior lower dose level. Safety data for at least 7 days post-dose from all the subjects at the prior lower dose will be reviewed before dose escalation.

The next cohort will open if all the patients in the previous cohort have been included and no safety issues have aroused during the follow-up after cell infusion (data of at least 7 days after cell infusion is required to proceed to each subsequent dose). Patients will continue to be followed for possible DLTs during the 21 days following cell infusion.

For phase II, eligible patients will be allocated to arm A or B considering HLA typing and within each arm they will then be randomized in a 1:1 ratio to 1 of 2 treatment groups (SoC or SoC+RP2D).

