1. STUDY OUTCOME MEASURES

## Primary outcome:

**Phase I**

The primary outcomes of the Phase I in this study are:

- The primary outcome will be the occurrence of DLTs in all patients during the study treatment, until 21 days after cell infusion, and the MTD.

DLT is defined as:

- - any grade 3 or higher toxicity with an attribution of definitely or probably related to the infusion of the cells and
  - any lower grade toxicity that increases to a grade 3 or higher as a direct result of the cell infusion.

Based on this, **RP2D** will be defined as: The recommended dose will be the MTD unless no MTD is determined in the dose escalation segment of the study. In the latter, the recommended dose will be the highest dose evaluated in the dose escalation segment.

- Incidence and nature of DLT of a single infusion of NK or memory T cells from a healthy donor recovered from COVID-19 (dose escalation).

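### For Phase I patients discharged early, the follow-up rules do not guarantee the examinations and blood tests that the 21-day DLT outcome and the 7-day escalation review require

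*Protocol*

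**What the plan says.** **What is required.** The Phase I primary outcome is the "occurrence of DLTs in all patients during the study treatment, until 21 days after cell infusion, and the MTD" (Protocol, Primary outcome, Phase I). Study design repeats the commitment: "The 18 patients in the Phase I will continue to be followed for possible DLTs during the 21 days following cell infusion". So do Administration dose and Schedule, Subject Treatment Assignment and Additional Assessments. For escalation, Subject Treatment Assignment states: "Safety data for at least 7 days post-dose from all the subjects at the prior lower dose will be reviewed before dose escalation". Table 2 marks physical examination, haematology and biochemistry at D7, D14 and D21. It also has a DLT row that starts at screening/D0 and runs across several visit columns.

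**What is guaranteed after discharge.** The Follow-up section says: "Patients will be followed up until day 90, discharge or death, whichever occurs earlier". For patients discharged before Day 30 it adds that "weekly ambulatory visits (days 7, 14, 21 and 28) will be performed if the investigator considers it appropriate". Daily Study Assessments also stop at discharge. The Additional Assessments section, which covers PCR, haematology, chemistry, immune markers and chimerism, opens with: "Will be performed as far as possible considering the increased work-load and if the investigator considers it appropriate". None of these passages makes an exception for Phase I.

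Two contacts after an early discharge are stated without that discretion in Follow-up: telephone calls at Day 30 and Day 90 that ask about adverse events, and donor chimerism sampling in all patients until donor cells disappear. Chimerism also appears under the discretionary heading of Additional Assessments.

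**The concern.** The protocol requires an outcome to be observed in every Phase I patient, but makes the visits that would observe it optional once the patient goes home. A site that follows the Follow-up section exactly can discharge a patient on, say, Day 5 and arrange no further examination or blood test inside the 21-day window, without departing from the protocol.

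This matters more in Phase I than elsewhere. These patients need no oxygen or at most 2.5 lpm at entry, so discharge before Day 21 is plausible, although the protocol gives no length-of-stay figure. A DLT is a toxicity of grade 3 or higher attributed to the cells, and laboratory toxicities cannot be graded without blood tests. Liver illustrates the point. Of GVHD the protocol says "It can involve skin, liver and gastrointestinal tract in the acute phase". It also states, in its section on risks to recipients, that the most serious complications usually fall in the first month after infusion, so Days 8 to 21 are not a period that can safely go unobserved.

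At stake is the Phase I primary outcome and, through it, the dose carried into a Phase II of 164 patients. When no MTD is found, the RP2D is the highest dose evaluated, so missed DLTs push the recommendation upward. The point does not concern the Phase II recovery endpoint.

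**Working it through.** **1. The stated count.** 3 patients × 3 cohorts × 2 arms = 18, and 18 + 164 = 182. Both agree with the Sample size section; no stated figure is wrong here.

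**2. Requirement against guaranteed source, for a Phase I patient discharged before Day 7.**

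| Need | Required by | Guaranteed after discharge? |
| --- | --- | --- |
| 7-day safety data, all subjects | Subject Treatment Assignment | Day 7 visit and bloods discretionary |
| Examination at D7, D14, D21 | Table 2 | Discretionary (Follow-up) |
| Haematology and biochemistry at D7, D14, D21 | Table 2 | Discretionary (Follow-up; Additional Assessments) |
| DLT status to Day 21 | Primary outcome; Study design | Only the Day 30 call, after the window |
| Chimerism | Follow-up; Table 2 footnote | Required in Follow-up, discretionary in Additional Assessments; detects donor cells, not toxicity, and stops once negative |

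Adverse-event collection runs only to each subject's final follow-up visit, so it does not fill the gap if that visit was the discharge.

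**3. Illustration of the effect.** The documents give neither a DLT risk nor an early-discharge rate, so everything here is assumed. Let p be the true 21-day DLT risk, m the number of the three patients who are incompletely observed, and f the share of their DLT risk that is still observed. Then

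P(at least one DLT seen) = 1 − (1 − p)^(3−m) × (1 − f·p)^m.

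At p = 20%:
- all three fully observed: 1 − 0.8³ = 0.488
- one wholly unobserved (m = 1, f = 0): 1 − 0.8² = 0.360
- one with half the risk still observed (m = 1, f = 0.5): 1 − 0.8² × 0.9 = 0.424
- two wholly unobserved (m = 2, f = 0): 1 − 0.8 = 0.200

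Across a range of assumed risks:

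| Assumed p | Full observation | One, half observed | One, unobserved | Two, unobserved |
| --- | --- | --- | --- | --- |
| 10% | 27% | 23% | 19% | 10% |
| 20% | 49% | 42% | 36% | 20% |
| 33% | 70% | 63% | 55% | 33% |

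These describe detection of any DLT over the full 21 days. They are not error rates for the escalation decision, which rests on data of at least 7 days.

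**The case against.** Four points can fairly be made against this.

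*Table 2 already contains the visits.* The limit at discharge is attached only to the daily D1–D90 column; D7, D14 and D21 stand as separate columns without it. This stands, and it makes the problem a contradiction between sections rather than an absent plan. It does not remove the problem, because the Follow-up text deals specifically with discharged patients and makes those same visits optional.

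*Escalation has its own gate.* Read as written, Subject Treatment Assignment keeps the next cohort closed until 7-day data exist for every subject. This stands. A reader might infer that escalation will proceed on incomplete data; the text does not support that. What remains is that the protocol names no mandatory source for those data after an early discharge, and that the gate does not extend to Days 8 to 21.

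*Nothing says that an unexamined patient is DLT-free.* Also correct. A reader might infer it from the rule that the next cohort opens if no safety issue has arisen, and from the RP2D default to the highest dose. No passage states it, however, and the definition of the DLT-evaluable set may properly sit in a SAP that is not shown. The protocol's silence on counting is therefore not itself the point; the optional visits are.

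*Other contacts exist.* The phone calls are not the only fixed contact, since Follow-up also requires chimerism sampling, and the Day 30 call can recover symptomatic events in retrospect. That reduces the loss. Neither contact supplies examination findings or laboratory grades within the window.

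It is also true that the protocol expects grade III to IV GVHD in fewer than 1% of patients. Liver is used here only as an example of toxicity that needs a blood test, not as a likely DLT.

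**Conclusion.** The conflict is real and rests on the text alone. Follow-up and Additional Assessments cannot both be applied as written and still guarantee what Study design, Subject Treatment Assignment, Table 2 and the Phase I primary outcome require. An early-discharged Phase I patient may have no examination or laboratory grading for part of the 21-day window, and the direction of the effect is towards too few observed DLTs. The 7-day escalation decision is protected if its rule is applied strictly; Days 8 to 21 are not.

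The size cannot be derived from the documents. It depends on the DLT risk, on how many patients go home early, on how many visits investigators choose to hold, and on what the Day 30 call recovers. The fall from 49% to 36% at an assumed 20% risk with one of three patients wholly unobserved is illustrative only. It shows why three-patient cohorts are sensitive: each patient is a third of the evidence. The case for correction rests on the low cost of closing the gap in the primary outcome, not on that figure.

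**What to change.** Reconcile the sections with two sentences, placed in Follow-up and cross-referenced from Additional Assessments:

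- For the 18 Phase I patients, the Table 2 assessments at Days 7, 14 and 21 (physical examination, haematology, biochemistry and adverse-event review) are performed whether or not the patient has been discharged; the investigator-discretion and workload qualifiers do not apply to them.
- A Phase I patient contributes to the 7-day escalation review, or enters the 21-day DLT denominator as DLT-free, only if the assessments due by that time were done.

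A phone contact by Day 21 may be added as a supplement, but it should not replace a visit, since it cannot provide laboratory grading. Follow-up and Additional Assessments should also agree on whether chimerism sampling is mandatory.

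The cost is a wording amendment and up to three outpatient visits per patient, at most 18 × 3 = 54 visits in total, all already in Table 2. The downsides are the burden on recovered patients and an occasional delay in opening a cohort while outstanding assessments are completed.

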## Study design

## Open label, multicenter, double-arm interventional randomized phase I/II clinical trial study.

This Phase I/II escalating-dose clinical trial is a randomized study to determine RP2D, safety, tolerability, alloreactivity and efficacy of cell therapy with allogeneic NK cells (arm A) and T memory cells (arm B) from blood donors who have recovered from COVID-19 and are currently disease-free.

Donors and patients will be HLA tested and allocated into two different arms:

- **Arm A**: If one or more HLA class I match between donor and recipient are present, patients will receive memory T cells.
- **Arm B**: If donor and recipient have less than 1 HLA class I match or HLA-KIR mismatch, they will receive NK cells.

There will be two consecutive phases in the study:

1. The first dose escalation segment focuses on determining safety and the recommended dose for the second segment.
2. Phase II focuses on efficacy and safety.

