**Phase II**

The primary outcome in Phase II in this study is:

- The incidence of patient recovery infusing adoptive NK cells or adoptive memory T cells.
- **Recovery is defined as:** Proportion of participants in each group with normalization of fever and oxygen saturation [criteria for normalization: temperature < 38°C armpit, and SpO2 > 94%, sustained for at least 24 hours] or lymphopenia recovery **through Day 14.**

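### The blood counts that can decide the Phase II primary outcome, and the Day 7 and Day 14 visits after discharge, are left to an unblinded investigator, against Table 3

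*Protocol*

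**What the plan says.** The trial is described as "Open label, multicenter, double-arm interventional randomized phase I/II clinical trial study" (Study design), and no blinded outcome assessor is mentioned.

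Under Primary outcome, Phase II, recovery has two routes. One is normal temperature and oxygen saturation; the other needs a blood count: "sustained for at least 24 hours] or lymphopenia recovery", through Day 14.

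Four places govern whether the data for these routes are collected:

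- **Additional Assessments** lists "Hematology and Chemistry: Day 3, 7, 14, 21, 28" under a heading that makes the whole list conditional: "Will be performed as far as possible considering the increased work-load and if the investigator considers it appropriate". Donor chimerism is in the same list.
- **Daily Study Assessments** covers temperature and oxygen saturation up to discharge, with a workload proviso: "these will be performed as far as possible considering the increased work-load".
- **Follow-up** sets the default end: "Patients will be followed up until day 90, discharge or death, whichever occurs earlier". For patients discharged before Day 30, "weekly ambulatory visits (days 7, 14, 21 and 28) will be performed if the investigator considers it appropriate". The contacts stated without discretion after early discharge are telephone calls at Days 30 and 90. On chimerism it adds: "Donor chimerism will be evaluated on days specified in the schedule of assessments and weekly until disappearance in all patients".
- **Table 3** (Schedule of activities phase II) ticks haematology at Days 7 and 14 and the evaluation of recovery at Day 14, with no footnote making them optional.

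**The concern.** The count behind one route of the primary outcome may or may not be taken, and the person deciding knows the treatment. Since the outcome is met if either route is met at any time up to Day 14, each further count is another chance to be scored as recovered. If one group is sampled more, its observed recovery rate rises even when true recovery is equal.

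More sampling of cell recipients is plausible. Repeat chimerism testing is triggered by persisting donor cells, which only they can have. The Day 7 decision on a second cycle rests partly on blood results, and only they can receive one.

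Also at stake is whether a patient discharged before Day 14 gets the Day 14 evaluation that Table 3 lists. The Statistical analysis paragraph compares recovery at the 14th day. If that is read as status on that day, a discharged patient who is not called back has no observed outcome.

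**Working it through.** **1. The provisions side by side**

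| Item | Table 3 | Text |
| --- | --- | --- |
| Haematology Day 3 | marked, in the column that runs until discharge | discretionary (Additional Assessments) |
| Haematology Days 7 and 14 | marked, no condition | discretionary (Additional Assessments) |
| Day 7 and 14 visits after discharge | columns marked for all | discretionary (Follow-up) |
| Evaluation of recovery, Day 14 | marked, no condition | no visit guaranteed after discharge (Follow-up) |

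The telephone calls at Days 30 and 90 cannot fill the gap: both fall after Day 14, and neither yields a count.

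**2. The plan's own figure**

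Inputs from Sample Size: one-sided alpha 0.05, beta 0.2, recovery 45% on standard of care and 0.45/0.7 = 64.29% on intervention. With pooled variance under the null and no continuity correction, where p̄ = 0.5464:

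n = [1.645·√(2·p̄·(1−p̄)) + 0.842·√(p1(1−p1) + p2(1−p2))]² / (p2−p1)² = 81.3, rounded up to 82 per comparison group.

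This matches the table. The protocol plans 82 per HLA arm, randomised 1:1, which is 82/2 = 41 per randomised group, so both sizes are carried below.

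**3. Effect of unequal sampling (illustration)**

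The protocol gives no visit or sampling rates. The following are assumptions:

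- true recovery is equal in both groups, and 45% is observed with cells;
- a share s of 10-20% is seen as recovered only through a discretionary count;
- that count is missed m = 10-30 percentage points more often in controls.

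The spurious gap d depends on what s is a share of:

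- share of recoveries: d = 0.45 × s × m, from 0.45 × 0.10 × 0.10 = 0.0045 to 0.45 × 0.20 × 0.30 = 0.027;
- share of all patients: d = s × m, from 0.10 × 0.10 = 0.01 to 0.20 × 0.30 = 0.06.

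Observed control recovery is 0.45 − d. The rejection probability of the one-sided 5% test is Φ[(d − 1.645·se0)/se1]. Here se0 = √(2·p̄·(1−p̄)/n), p̄ is the mean of the two observed rates, and se1 is the unpooled standard error.

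Worked case, d = 0.027 and n = 82: rates 0.450 and 0.423, p̄ = 0.4365, se0 = 0.07745, se1 = 0.07743. Then (0.027 − 1.645 × 0.07745)/0.07743 = −1.297, and Φ(−1.297) = 0.097.

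| Meaning of s | Gap d (points) | Type I error, 41 per group | Type I error, 82 per group |
| --- | --- | --- | --- |
| no difference in sampling | 0 | 5.0% | 5.0% |
| 10-20% of recoveries | 0.45-2.7 | 5.4-8.1% | 5.6-9.7% |
| 10-20% of all patients | 1-6 | 6.0-13.6% | 6.5-19.3% |

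The second reading is the stronger assumption: 10-20% of all patients at 45% recovery is 0.10/0.45 to 0.20/0.45, or 22-44% of all recoveries.

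**The case against.** The strongest reply is that the text treats the groups alike. Table 3 is one schedule for both. Follow-up asks for chimerism in all patients, and Additional Assessments lists chimerism under the same discretionary heading as haematology, so it is no firmer a reason to recall anyone. Day 7 improvement is a secondary outcome not restricted to cell recipients. Discharge is also a listed ground for discontinuing study medication, which weakens the second cycle as a reason for visits after discharge.

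This stands against a reading that a reader might infer: that controls have no reason to be sampled and that the bias must favour the cells. The documents do not support that. The opposite is possible too: counts are easiest to obtain in hospital, so if cell recipients went home sooner they might have fewer.

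It is also fair that the post-discharge visit is the weaker half of the point. Temperature and saturation are assessed daily until discharge, workload permitting, and many discharged patients will already have met that route. A later visit cannot change their cumulative result. The exposed part is the lymphocyte count, which is discretionary in hospital as well.

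Finally, a reader might infer that no analysis could repair missing counts. That is too strong. Missingness that depends on treatment alone can be handled within group, and an unseen SAP may say how. The difficulty arises if missingness also depends on the unobserved outcome, because any remedy then rests on untestable assumptions. Whether the measurement is taken at all is a protocol rule, and here it is stated two ways.

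**Conclusion.** The point holds as an internal contradiction with a possible bias attached. Additional Assessments and Follow-up make data for the primary outcome discretionary in an open-label trial, while Table 3 makes them part of the schedule. Unequal sampling can then produce a difference without a treatment effect.

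Its direction and size are not established. The figures of 5.4-9.7% and 6.0-19.3%, spanning both group sizes, rest on assumed shares and sampling gaps and on the choice of base; they show sensitivity and are not a forecast. If the groups are sampled alike, the error stays at 5.0%. The point should be corrected because it concerns the primary outcome and the correction is cheap. Confidence is medium, since the share of patients whose result turns on a discretionary count is unknown and may be small.

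**What to change.** Reconcile Additional Assessments and Follow-up with Table 3 by removing the discretion for primary-outcome data:

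- require the lymphocyte count on Day 3 while the patient is in hospital, and on Days 7 and 14 (±1 day, the window already in Table 3), in both groups, discharged or not;
- require the Day 14 evaluation of recovery in every patient;
- let only counts from these scheduled days enter the primary outcome, so that extra samples taken for other reasons add no chances of recovery.

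Discretion can stay for exploratory samples and for visits after Day 14.

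The change should not go further than this without acknowledging new burden. Day 3 after discharge is not a scheduled visit, and respiratory status is blank at Day 7 in Table 3. A single outpatient reading also cannot show that temperature and saturation were normal for 24 hours.

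The cost is a wording change and some extra site workload for patients discharged before Day 14, for counts and an evaluation that Table 3 already lists. The sample size does not change.
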